## Abstract

Background

People with visual impairment (VI) tend to face more psychological distress than normally sighted individuals due to mobility restrictions, fear of falling, and sleep disturbances. However, research to address these problems is rare. This study aims to investigate the effect of mindfulness-based yoga versus physical exercise on the psychological well-being of individuals with VI.

Methods

This study will be a single-blinded, three-armed, multicentered, randomized controlled trial (RCT). A total of 132 participants with VI (ages 15-25) will be recruited in the study and will be randomly assigned to either group 1 (mindfulness-based yoga), group 2 (physical exercise), or group 3 (wait-list control). Groups 1 and 2 will receive intervention for 40 hours (eight weeks, weekly five days, one hour/day), whereas group 3 will continue their daily activities as usual. The intervention will take place in the afternoon from Monday to Friday. The timing varies between 4-5 pm according to the different time schedules of the institutions of the blind. Three times, assessments will be conducted at T0 (baseline), T1 (eighth week at the completion of the intervention), and T2 (sixth month following the completion of the intervention). ANOVA will be used to find out the differences between groups; repeated measures ANOVA will be used to check within-group changes.

Trial status

The study was first screened in December 2021. The recruitment of participants has been completed in two centers covering 62 individuals with VI, and intervention started in August 2022. The data collection is still ongoing due to the nature of the study design, a specific demographic, complex logistics, and administrative bottlenecks. The study incorporates three different groups and a substantial sample size (n=132). The specific demographic, people with visual impairments, are rare and difficult to locate. In addition, a six-month follow-up assessment contributes to complex procedures while coordinating between various institutions and securing necessary authorizations.

Discussion

This study will be the first comprehensive RCT to investigate the psychological well-being of the VI population with various psychophysiological and hormonal parameters in multiple centers. The presence of physical exercise and a wait-list control group will further elucidate the potential mechanism of Mindfulness-based yoga. Mindfulness-based yoga can be integrated into educational and rehabilitation systems to enhance the well-being of individuals with VI.

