**Figure 1 FIG1:**
[figure not shown]
Consolidated Standards of Reporting Trials (CONSORT) flow diagram of the study T0 - baseline; T1 - at the perception of intervention (eight weeks); T2 - six months following the intervention

**Table 1 TAB1:** Standard Protocol Items: Recommendations for Interventional Trials (SPIRIT) HADS,- Hospital Anxiety and Depression Scale; OHQ - Oxford Happiness Questionnaire; ECG - electrocardiograph; HRV - heart rate variability; RR - respiratory rate; GSR - galvanic skin resistance; EMG - electromyography; TUG - Time Up and Go Test; 30CST - 30-second Chair Stand Test; MSPSS - Multidimensional Scale of Perceived Social Support; HWS - Holistic Well-being Scale; VisQoL - Vision Quality of Life Index; PSQI - Pittsburgh Sleep Quality Index; T0 - baseline; T1 - at the completion of intervention (eight weeks); T2 - six months following the intervention

	Enrolment	Allocation	Post-allocation			
Timepoint	0	0	T0	Intervention	T1	T2
Enrolment						
Eligibility screen	X					
Ophthalmology test		X				
Oral Informed consent with fingerprint	X					
Allocation		X				
Interventions						
Mindfulness-based yoga				X		
Physical exercise				X		
Wait-list control				X		
Assessment						
Sociodemographic characteristics			X			
HADS, OHQ, biomarkers, ECG, HRV, RR, GSR, EMG, TUG, 30 CST, MSPSS, HWS, VisQoL, PSQI			X		X	X
Treatment-related Information: adverse events, adherence to assigned treatment			X		X	X
Potential confounders: food			X		X	X

Objectives and hypothesis

The objectives will be as follows: to investigate the effect of mindfulness-based yoga (MY) on 1) psychological well-being, 2) physical well-being, 3) physiological well-being, 4) spiritual well-being, 5) health-related quality of life, and 6) sleep quality in individuals with early moderate-to-severe visual impairment and blindness.

We hypothesize that 1) the MY program will effectively improve psychological well-being, physiological well-being, physical well-being, social well-being, spiritual well-being, vision-related quality of life, and sleep quality in individuals with early VI, and 2) the MY will be superior to PE in improving psychological well-being, physiological well-being, physical well-being, social well-being, spiritual well-being, vision-related quality of life, and sleep quality in individuals with early VI.

Design

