Inclusion and exclusion criteria

Inclusion criteria include the following: 1) a clinical diagnosis of early VI, with a visual disability severity rating of moderate-to-severe VI according to WHO International Disease Classification 11 Distance Visual Impairment [48]; 2) age between 15-25 years old; 3) early visual impairment, early VI refers to people who have been blind since birth or early childhood (<5 years), whereas late VI indicates persons who lost sight after learning to read print [49]; (4) participants who are willing to give oral consent or assent along with a thumbprint. For participants under 18 years old, a consent form signed by their legal guardian will be needed as well.

Exclusion criteria are the following: 1) participants who are receiving treatment for mental disorders currently or with uncontrolled mood disorders; 2) current participation in any other pharmacological trial or cognitive behavioral program; 3) cognitive impairment such as mental retardation; 4) other debilitating medical conditions except VI, such as having a hearing impairment, epilepsy, or physical disability (e.g., deformity of limbs), that can impede full participation in the study; 5) having a secondary VI, such as Grave's ophthalmopathy (thyroid eye disease), Bechet syndrome (blood vessel inflammation throughout the body), uveitis (inflammation of the middle layer of the eye), multiple sclerosis (autoimmunity), in which symptoms are caused by a different system disorder or another illness [23].

The inclusion criteria are to maximize the enrolment of appropriate participants, while the exclusion criteria are used to screen out participants who are with medical conditions for which yoga or exercise is contraindicated, which pose a safety risk, preclude fully informed consent, or hinder compliance with interventions (e.g., mental retardation).

Sample size

A previous study on children (9-16 years) with VI reported a moderate effect size of 0.4 for overall well-being [37]. To anticipate a similar effect size of at least 0.4 on adolescents and young adults (15-25 years) and using the software G Power 3.1 with 80% power at a 5% level of significance, 36 subjects will be in each arm of the study. Considering an attrition rate of 20%, we will recruit 132 subjects, with 44 per arm.

Interventions

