## Results

Data will be collected and extracted using the standard procedure. The appropriate statistical test will be conducted to analyze the above-mentioned variables using SPSS V. 22.0 software (IBM Inc., Armonk, New York). To find out the differences between groups, an ANOVA test will be adopted; to check within-group changes, a repeated measures ANOVA will be used. The findings will be released subsequent to the study of the data.

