The strengths of this research are: 1) subjective psychological questionnaires correlating with objective, evidence-based assessment will strengthen the study design; 2) multiple centers with a large sample size in different geographical areas will support generating the findings of this research; and 3) a three-group study design will enhance the strength of the study. The active control group (PE group) will be compared with the experimental group (MY group) to discover the potential mechanisms of yoga, especially the effects of mindful awareness on psychological well-being. The wait-list control group will be compared with the other two to reveal the significance of either type of physical activity contributing to general well-being.

Limitations

Potential limitations and their related strategies need to be acknowledged. Subject dishonesty might happen during the interview process to protect one's privacy and social identification, as they might appear to have prosocial behaviors toward interviewers. To ameliorate the effects of bias, the interviewers will inform the participants that private information will be kept confidential, and the interview will be in the form of a one-on-one session. It is crucial to keep in mind that despite the study's design using numerous centers and a sizable sample size from various geographic regions, regional-specific factors like cultural differences, resource accessibility, and customs may still have an impact on the findings. However, in this study, stratified randomization will be adopted to minimize the potential effects of confounding factors such as location, population, educational and cultural differences where the research will take place. Since each center shares certain similarities in terms of setting, such as food habits, living standards, teaching methods, and cultural background, it is reasonable to expect that various confounding factors will have the minimum effects on the results. Additionally, this study will investigate the evaluation and implementation of the MY or PE protocol. However, social support will not be considered as one factor for randomization. Therefore, it will be possible if there will be varying levels of social support among the three groups. Dropouts and missing data may also pose a risk to internal validity. The strategy to reduce the dropout rate has been discussed previously in the section named "attrition and missing data".

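### The only between-group test named, a three-arm ANOVA, does not test the hypothesis that yoga is superior to exercise, and no deciding visit is named

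*Protocol article*

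**What the plan says.** **Test.** The Abstract (Methods) states "ANOVA will be used to find out the differences between groups". The Results section says the same: "To find out the differences between groups, an ANOVA test will be adopted". Both places assign repeated measures ANOVA to changes within groups, so no group-by-time term is planned as a between-arm test. Multivariable regression appears under Attrition and missing data, only as a way to control confounding.

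**Hypotheses.** Objectives and hypothesis has two: that MY is effective, and that "the MY will be superior to PE in improving psychological well-being" and the other domains. The second is pairwise and directional.

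**Intended comparisons.** Under Strengths in the Discussion: "The active control group (PE group) will be compared with the experimental group (MY group"), and the wait-list is to be compared with both other arms. No test is attached to either statement.

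**Visits.** Outcomes are measured at T0, T1 (eight weeks) and T2 (six months after the intervention ends). The hypotheses, sample size, outcomes and analysis text do not say which post-baseline visit decides the main claim.

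**Size.** Sample size cites a study that "reported a moderate effect size of 0.4 for overall well-being", then "using the software G Power 3.1 with 80% power at a 5% level of significance", giving "36 subjects will be in each arm of the study". It adds: "Considering an attrition rate of 20%, we will recruit 132 subjects, with 44 per arm". Whether 0.4 is Cohen's f or a standardised mean difference is not stated.

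**The concern.** The named test and the hypothesis ask different questions. The F test asks whether any of the three means differ. It has no direction, and it can be significant solely because the untreated arm did worse than both active arms. Hypothesis 2 asks whether MY does better than PE.

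If a significant ANOVA were taken as the trial's positive result, it could be reported as support for yoga over exercise when the data show only that either activity beats no activity. The PE arm was added precisely to separate those two explanations.

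Two post-baseline visits without a ranking add a second gap: a claim at either one would be consistent with the text.

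**Working it through.** **Inputs from the article:** three arms, 1:1:1, 36 evaluable per arm (108 in total), 44 recruited per arm, alpha 5%, effect size 0.4 of unstated metric. **Assumed here:** common SD of 1, normal outcomes, one score at one visit, MY = PE, and both better than wait-list by d.

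**1. The plan's own figure.** A one-way ANOVA with f = 0.4 needs 22 per arm for 80% power; 36 per arm would give 96.5%. A two-sided two-sample t test at d = 0.4 needs 100 per arm. Neither gives 36, so the sample size does not reveal which test or metric was meant. For attrition, 36 × 1.2 = 43.2, rounded up to 44. The origin of 36 is a separate matter and does not decide this point. Both readings of 0.4 are carried below.

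**2. How often F is significant with no MY advantage.** With means (d, d, 0) the variance of the three means is 2d²/9, so f = d√2/3. The noncentrality is λ = f² × 3n = 2nd²/3. The test rejects when F exceeds its 95% point, which is 3.08 on 2 and 105 df at n = 36.

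| d (SD) | f | λ (n = 36) | P(significant), 36 per arm | 44 per arm |
|---|---|---|---|---|
| 0.3 | 0.141 | 2.16 | 24% | 28% |
| 0.4 | 0.189 | 3.84 | 39% | 47% |
| 0.5 | 0.236 | 6.00 | 57% | 67% |
| 0.6 | 0.283 | 8.64 | 74% | 83% |
| 0.8 | 0.377 | 15.36 | 94% | 98% |
| 0.85 | 0.400 | 17.28 | 96.5% | 98.8% |

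The rate passes 50% at d of about 0.46 with 36 per arm. In every row the true MY-PE difference is zero. A direct MY-PE contrast would be significant in about 5% of such trials.

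**3. Two visits.** Take one null contrast tested at two-sided 5% at T1 and at T2, with a claim allowed if either is significant. Simulation gives an error of about 8% at a visit correlation of 0.7 and about 9% at 0.4. Both correlations are assumed.

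**4. What the direct contrast can detect.** With 36 per arm the noncentrality is d√(36/2) = 4.243d.
- d = 0.67: 2.84, two-sided 5% power 80% on 105 df.
- d = 0.4: 1.70, power 39%.

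**5. What a gate costs.** Simulated at a true MY-PE difference of 0.67 SD, 36 per arm:

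| Wait-list mean relative to PE | MY-PE contrast, ungated | Gated on MY versus wait-list | Gated on significant F, then unadjusted pair |
|---|---|---|---|
| Equal to PE | 80% | 69% | 76% |
| 0.3 SD worse than PE | 80% | 80% | 80% |

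**The case against.** The strongest reply is that a journal article gives a one-line analysis summary, and that post-hoc tests and multiplicity rules belong in a fuller document that is not shown. The Discussion plainly intends the pairwise comparisons, so ANOVA followed by pairs is a natural reading, and nothing says a significant F will be read as MY beating PE. Much of this stands. The missing post-hoc procedure is not the point. What remains is that the article does assign a test to the between-group question, and that test does not match its own hypothesis.

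Four stronger readings are tempting but unsupported:

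- **The F test will usually be significant when MY equals PE.** That depends on an effect size the article does not settle. It holds if 0.4 is Cohen's f (96.5%), but not if 0.4 is a standardised difference (39% with 36 per arm, 47% with 44).
- **No MY-PE comparison is planned.** The Strengths paragraph says one is.
- **The type I error is inflated as the plan stands.** The 8% to 9% presumes a rule of claiming at whichever visit succeeds, and the article states no such rule. It shows what naming a visit would prevent.
- **Planned contrasts in sequence gain power.** The 80% at 0.67 SD belongs to an ungated contrast. In the two cases simulated, the sequence does no better than F followed by unadjusted pairs, and it does worse when PE is inert.

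**Conclusion.** The point holds in limited form. A significant result on the only between-group test named would not establish hypothesis 2, the article ties no test to the MY-PE comparison it intends, and neither visit is decisive. This mismatch does not depend on any effect size.

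How often it could mislead does. The range is about 24% to 94% of trials for assumed equal benefits of 0.3 to 0.8 SD over wait-list with 36 per arm, and 96.5% on the Cohen's f reading. These figures assume a common SD, normality and a single visit. The conclusion concerns which test carries the main claim; it does not show that the trial will draw the wrong inference.

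**What to change.** Name one HADS score (anxiety, depression or total) and one deciding visit, for example T1. For that score and visit, let the main claim rest on two pre-specified contrasts instead of the omnibus F, each at two-sided 5%: MY versus wait-list first, then MY versus PE only if the first is significant. Make PE versus wait-list, all T2 contrasts and the other listed outcomes secondary. Fix this before any between-arm results are seen.

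**What it secures.** Familywise error of 5% for that one score and visit. It does not cover the Oxford Happiness Questionnaire and the five biomarkers, which the article also lists as primary; making them secondary is a real choice that must be stated.

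**What it costs.** No change to data collection. T2 is no longer a route to the main claim, and MY versus PE cannot be claimed if MY fails against wait-list. The gate can lower power for MY versus PE: about 69% against 80% ungated at a true 0.67 SD if PE equals wait-list. At a true difference of 0.4 SD even the ungated contrast has only about 39% power with 36 per arm, so the change makes the question answerable in form without making the trial larger.

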## Introduction

People with visual impairment (VI) face a higher risk of psychological distress, which affects their multidimensional health aspects [1]. The mortality rate among the visually impaired is much higher than that of normally sighted people [2]. Visual impairment, characterized by low vision or blindness, is a functional limitation of the eyes. At least 2.2 billion people worldwide are visually impaired, and this is gaining growing concern in the development of public health policies [3]. Based on global population growth and increased life expectancy, it is estimated that global blindness will triple and moderate-to-severe VI will double by the year 2050 [4]. Though VI affects hundreds of millions globally, 90% of those with VI live in low- and middle-income countries [5]. India contributes 8 million people with blindness and 62 million with VI to the global population [6]. 

Loss of vision affects various aspects of life, such as reduced physical activities, unintentional injuries, loneliness, disturbed sleep, and low self-esteem [7-12]. Compared with the general population, people with VI are at a higher risk of experiencing psychological distress, such as anxiety and depression [13,14]. In return, the accumulated stress can lead to more vision loss [15]. Various factors contribute to psychological distress in the visually impaired, such as poor social communication, compromised daily role functions, and self-care capacities [16-19]. In addition, they face a higher chance of unemployment and more stress from family responsibilities and marriage expectations than their sighted peers [20-22]. Psychological distress in VI induces fatigue, low self-esteem, caregiver distress, and socioeconomic burden at large [23-26]. In addition, people with VI, especially those with no perception of light, tend to experience poorer sleep quality than the sighted due to the desynchronized rhythm of melatonin secretion [11]. Sleep disturbance is a mediating factor in mental health, and sleep management has been used as an effective strategy to treat mental disorders [27].

Even though individuals with VI encounter a high incidence of mental distress, the challenge they face is hardly noticed and barely resolved [1,28]. The pharmacological management of anxiety, depression, and insomnia is complicated because of its adverse effects, as antidepressants might provoke agitation, nervousness, suicidal thoughts, and even reduce eyesight in partially blind [29]. Hence, adopting a complementary and alternative management (CAM) approach to address the adverse and limited effects of pharmacological management is essential. It has revealed its positive impact on reducing negative emotions and stress hormones and increasing self-control, positive emotions, sleep quality, and immune reactivity [30-32]. Mind-body exercise is one of the most extensively practiced non-pharmacological treatments for its gentle and low-risk nature [33-35]. Yoga, promoted by the United Nations and welcomed by the whole world [36], has a beneficial impact on physical outcomes in the population with VI [37,38]. Mindfulness-based yoga (MY) integrates mindful awareness into traditional yoga practices, combining mindful awareness to enhance self-awareness, focus on the present moment, and cultivate a non-judgmental attitude by paying attention to bodily sensations, thoughts, and emotions [35]. Apart from that, MY encourages practitioners to extend the practice of being present beyond yoga mats into their daily lives, creating a profound impact on their overall well-being [39]. Mindfulness-based yoga is a valuable component of complementary and alternative management, providing a holistic approach to a sense of well-being by blending the physical benefits of yoga with the mental, emotional, and spiritual benefits of mindful awareness.

Most of the previous research has explored populations with VI who are either middle-aged or old adults (above 45 years) or children (below 16 years) [37,38]. However, adolescents and young adults (15-25 years) with VI have largely been neglected despite facing unique challenges in academics and complex life situations [40,41]. This age group contends with pressures related to future job opportunities, relationships, and academic performance [42-44]. Mindfulness-based yoga, a practice aimed at mastering mind fluctuations, offers a profound solution for these challenges, starting from physical postures (asana), merging through breath regulation (pranayama), and reaching a sense of wellness and a peaceful state of meditative mind (dhyana). Mindfulness-based yoga nourishes inner well-being and resilience, helping this age group to manage stress effectively [45,46]. Therefore, to fill the research gap, this study will investigate the effects of MY in addressing psychological distress in adolescents and young adults with early VI. To enhance the internal validity, some participants will be randomly assigned to the physical exercise (PE) group since it only focuses on the physical dimension of well-being. The dosage of PE will be the same as that administered in the MY group.

## Materials and methods

A single-blinded randomized controlled trial (RCT) will examine the effects of MY versus PE to investigate the psychological well-being, physiological well-being, physical well-being, social well-being, spiritual well-being, vision-related quality of life, and sleep quality of students with early VI. This trial is designed according to the Consolidated Standards of Reporting Trials (CONSORT) statement (Figure 1) and reported according to the Standard Protocol Items: Recommendations for Interventional Trials (SPIRIT) statement (Table 1).

